#### Experimental (Intervention) Group

This group will receive the same standard of care as the control group at each hospital, which consists of immobilization for 7 to 8 weeks after the time of the injury or surgery, followed by hand therapy sessions for 10 weeks to manage scar tissue, sensory alterations, and edema. The experimental group will use the FEPSim device for therapeutic activities to increase strength, range of motion, and dexterity. For this group, the sessions’ length and frequency will depend on the patients’ needs and diagnoses. The length of each session will be between 30 minutes and 45 minutes, and they will be carried out once or twice per week.

### Outcome Variables

#### Primary Objective and Secondary Objectives 1 to 4: Primary Outcome Variables

The retention rates and intervention compliance will be calculated for the primary objective. The retention rates will be calculated according to the participants’ discontinuation of the interventions and their absence at the posttest at week 10. Intervention compliance means all of the hand rehabilitation sessions are completed by each group [21]. This study’s primary outcome variables for secondary objectives 1 to 4 are related to range of motion and strength: (1) AROM and PROM of wrist flexion and extension and forearm pronation and supination, (2) grip strength, and (3) pinch strength.

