**Methods:**

The trial will use a randomized controlled design comprising 47 intervention participants and 47 control group participants. Participants will be adults (age≥18 years) attending outpatient rehabilitation with limitations in their forearm, wrist, or hand function due to distal radial or ulnar fractures, stroke, or osteoarthritis. This study’s primary outcome variables are related to patients’ range of motion and strength, specifically active and passive wrist flexion and extension range of motion; active and passive forearm pronation and supination range of motion; grip strength; and pinch strength. The secondary outcome variables are related to patients’ perceived wrist pain and disability in activities of daily living. The patients’ perceived wrist pain and disability in activities of daily living will be measured using the patient-rated wrist evaluation questionnaire. The control group will receive the standard of care at each of the 2 hospital facilities (Glenrose Rehabilitation and Royal Alexandra Hospitals). The intervention group will receive the same standard of care as the control group at each facility and will use the FEPSim device for therapeutic activities to increase strength, range of motion, resistance, and dexterity. All the participants will be assessed at baseline (week 0); weeks 2, 4, and 8; and postintervention (week 10).

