### Evaluation Objectives and Research Questions

FEPSim has not yet been tested in a health care setting; therefore, a trial of the effectiveness of FEPSim in upper extremity rehabilitation is warranted. The primary objective of this study is to assess the feasibility of conducting a definitive trial in terms of recruitment, eligibility criteria, the type and number of diagnoses included, the length and dosage of the intervention, and the data collection methods. This study also aims to gather clinical and statistical information as well as information related to the costs and usability (adoption) of the new technology used in this study. Thus, this study has 6 secondary objectives:

To explore the clinical effectiveness of adding the FEPSim device to the standard of care for patients with injuries and clinical conditions of the forearm, wrist, and hand.To assess the outcome measures for measuring changes in the dependent variables.To gather and synthesize the data, from which the sample size of a definitive randomized controlled trial (RCT) can be estimated.To measure the key outcome domains (for completion rates, missing data, estimates, variances, and 95% CI for the differences between the intervention and control groups) for patients with injuries and clinical conditions of the forearm, wrist, and hand.To examine the total and component costs associated with the FEPSim device and with standard of care interventions for patients with injuries and clinical conditions of the forearm, wrist, and hand from an institutional perspective (ie, hospitals).To investigate the usability of the FEPSim device by therapists.

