#### Exclusion Criteria: Participants (Patients)

Outpatients will not be included in our study if they (1) have chronic regional pain syndrome as these participants’ baseline measurements would differ too much and they would experience abnormal pain responses; (2) report subjective or patient limitations that prevent them from participating (eg, excessive pain and edema); (3) are unable to participate in the program (outpatient hand clinic) twice a week (eg, transportation and limited buy-in); (4) have limitations in their reading and listening comprehension of the English language that prevent them from understanding the patient-rated wrist evaluation (PRWE) questionnaire; or (5) have limitations in following instructions due to a severe cognitive impairment.

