#### Control Group

This group will receive the standard of care at each hospital, which consists of immobilization for 7 to 8 weeks (for fractures) after the time of the injury or surgery, followed by hand therapy sessions for 10 weeks to manage scar tissue, sensory modifications, and edema as well as therapeutic activities to increase strength, range of motion, and dexterity. These therapeutic activities will be carried out using the equipment and materials available at each hospital, including weights and elastic or gripping equipment and materials. The sessions’ length and frequency will depend on the patients’ needs and diagnoses. The length of each session will be between 30 minutes and 45 minutes, and they will be carried out once or twice per week.

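### Compliance is defined as all-or-none over a session count that varies by patient, and retention puts stopping treatment and missing the week-10 assessment into one definition

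*Protocol article*

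**What the plan says.** The section on primary outcome variables states that "The retention rates and intervention compliance will be calculated for the primary objective". It then defines the two outcomes.

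- **Compliance:** "Intervention compliance means all of the hand rehabilitation sessions are completed by each group".
- **Retention:** calculated from participants' "discontinuation of the interventions and their absence at the posttest at week 10".

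The descriptions of both arms let session length and frequency depend on need and diagnosis. Therapy consists of "hand therapy sessions for 10 weeks", and of the sessions it is said that "they will be carried out once or twice per week". The exclusion criteria, however, rule out patients who "are unable to participate in the program (outpatient hand clinic) twice a week".

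The Data Analyses section adopts intention-to-treat and says that retention and compliance will help calculate the sample size of the definitive trial. In that sentence it links them to the secondary objectives, whereas the outcome section links them to the primary one. The section on withdrawal says that information from withdrawn participants is not used in the analysis.

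The labels also differ. The abstract says without qualification that the study's "primary outcome variables are related to patients" range of motion and strength, and Table 1 lists these measures as the primary outcome. The outcome section limits that status to secondary objectives 1 to 4, and Data Analyses calls clinical effectiveness a secondary objective.

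**The concern.** A compliance measure should show how much of the intended treatment patients took up. An all-or-none rule also reflects how many sessions they were given: the more sessions, the more chances to miss one. Session number depends on diagnosis, and the primary objective is to "assess the feasibility of conducting a definitive trial in terms of recruitment, eligibility criteria, the type and number of diagnoses included". A difference in compliance between diagnoses could then be read as a difference in acceptability when it only reflects the schedule.

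The unit is also unclear. Read literally, the sentence makes the group compliant or not, which yields no rate at all.

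For retention, stopping treatment and lacking outcome data are different events. The dropout allowance of the next trial depends on the second. If the two are counted together, the allowance may be too large. If withdrawn participants are removed from the count, it may be too small.

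**Working it through.** The article gives no expected value for compliance. For retention, the nearest figure is the 30% dropout in the Sample Size section: 94 × 0.30 = 28.2, so about 28 lost and 66 kept, and 66/94 = 70.2%.

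**Compliance**

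1. Sessions per patient: 10 weeks × 1 = 10, and 10 weeks × 2 = 20.
2. If each visit is attended with probability p, independently, the share completing all k sessions is p^k. The values of p are assumptions.

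| Attendance per visit | All of 10 | All of 20 |
|---|---|---|
| 90% | 0.90^10 = 35% | 0.90^20 = 12% |
| 95% | 0.95^10 = 60% | 0.95^20 = 36% |
| 98% | 0.98^10 = 82% | 0.98^20 = 67% |

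3. In each row, attended over scheduled has the same expected value in both columns, namely p. Only the all-or-none measure moves.
4. Effect of clustering: let half the patients attend every visit and half attend 90% of visits, so that the mean is still 95%. Completion of all sessions is (1 + 0.349)/2 = 67% for 10 sessions and (1 + 0.122)/2 = 56% for 20. The gap falls from 60 − 36 = 24 points to 67 − 56 = 11 points. It shrinks but keeps its direction.
5. Literal group reading: an arm of 47 has at least 47 × 10 = 470 visits. Even at 98% independent attendance, 0.98^470 is below 0.0001, so no arm would ever count as compliant.

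**Retention**

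The article does not say how the expected losses split, so the splits below are assumptions that show the range.

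1. If none of the 28 lost attended week 10, assessed retention is 66/94 = 70%. If half (14) had only stopped treatment and were assessed, it is (66 + 14)/94 = 80/94 = 85%. If all 28 were assessed, it is 94/94 = 100%.
2. The inflation of the next trial's sample size follows: 94/66 = 1.42 in the first case and 94/80 = 1.18 in the second.
3. The withdrawal rule pulls the other way. If none of the 28 was assessed but 14 were withdrawals removed from the denominator, apparent retention is 66/(94 − 14) = 66/80 = 83%. If all 28 were removed, it is 66/66 = 100%. The true figure in both cases is 70%.

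**The case against.** The strongest reply is that the definitions are loosely worded rather than wrong. The compliance sentence cites a source and may compress a fuller definition, so the participant-level all-or-none rule is one reading of it. The attendance rates are assumed, and missed visits usually cluster in the same people, which softens the effect. Both arms follow the same frequency rule and randomisation is stratified by condition, so session number should not systematically distort the comparison between arms. For retention, two components are named, but nothing says they must be added into one count.

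Much of this stands. It limits the compliance problem to the level of the figure and to comparisons between diagnoses, and makes the effect possible rather than certain. It does not rescue the definition, because neither the literal group reading nor the participant reading gives a usable rate. It also leaves open which retention figure would go into the next sample size.

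A reader might infer that the primary objective cannot be answered. The article does not support that. It plans summaries of treatment length and dosage, missing data and completion rates, has therapists record sessions in both arms, states a recruitment target (94/167 = 56.3%), and follows reporting guidance for feasibility trials. A reader might also object that no value separates feasible from not feasible. A condensed article may leave such criteria to the full protocol, so their absence here is no finding. Nor would the plan's own figures make good thresholds: 70% retention is simply the value expected after 30% dropout, and 167 counts potentially eligible patients.

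**Conclusion.** The concern holds for the two definitions. As written, compliance depends on the number of sessions prescribed as well as on attendance. In the illustration with 95% attendance and independent visits, it is 60% for 10 sessions and 36% for 20; in the clustered example with the same mean, 67% and 56%. These sizes rest on assumed attendance and on missed visits not being made up. The direction does not depend on the attendance rate chosen, as long as it is the same for both schedules and below 100%.

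Retention is ambiguous between treatment continuation and outcome assessment. The size of the resulting error cannot be known from the article, since it depends on how losses split.

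The label in the abstract and Table 1 is an editorial mismatch with the Methods. It does not change what can be estimated.

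**What to change.** 1. Define compliance per participant as sessions attended divided by sessions scheduled for that participant, and summarise it by arm and diagnosis. Keep the sessions scheduled after a participant stops treatment in the denominator; otherwise early stoppers would look compliant.
2. Define retention as randomised participants with a week-10 assessment divided by all randomised. Withdrawn participants stay in the denominator despite the withdrawal rule; this needs only the number randomised, not their data.
3. Report discontinuation of treatment as a separate rate over all randomised, and base the definitive trial's dropout allowance on the retention rate in item 2.
4. In the abstract and Table 1, mark range of motion and strength as primary outcomes for secondary objectives 1 to 4. State in Data Analyses that retention and compliance serve the primary objective.
5. Reconcile the twice-weekly attendance in the exclusion criteria with the once-or-twice-weekly sessions in the arm descriptions, since the number of scheduled sessions depends on it. Which of these is right is for the investigators.

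The cost is small. Therapists already record session frequency and length, and week-10 assessments are already planned. The one new item is a count of scheduled sessions per participant, kept as sessions are booked. The rest is wording.

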#### Primary Objective and Secondary Objectives 1 to 4: Secondary Outcome Variables

The secondary outcome variables are the patients’ perceived wrist pain and disability in activities of daily living.

#### Primary Objective and Secondary Objectives 1 to 4: Confounding Variables

The confounding effects of the participants’ age, gender, and medical condition (distal radial or ulnar fractures, stroke, or osteoarthritis); whether the participants are taking any pain medication; what activities the participants perform at home or work; and the therapist providing the intervention will be determined.

#### Secondary Objective 5: Estimating the Costs and Resource Use

This study aims to ascertain which factors result in differences in costs or outcomes when comparing the standard of care with the FEPSim device. The estimated costs of the interventions will be from an institutional perspective, that is, the Glenrose Rehabilitation and Royal Alexandra Hospitals. To estimate the resource use and costs, we will use a single study–based economic evaluation approach (patient-level data). The costs will include resources related to the following categories [19]: cost of the time spent by the human resources (hand therapists and support personnel, if applicable) involved in each of the interventions; this time will be converted to cost based on the average salary for each level of staff. It will also include the time human resources spend on the training sessions, learning to use the FEPSim device (ie, training sessions), and seeking technical support (in the intervention group).

#### Secondary Objective 6

We will determine the usability and technology acceptance of the FEPSim device based on the Unified Theory of Acceptance and Use of Technology constructs, that is, performance expectancy (FEPSim was useful); effort expectancy (learning to use FEPSim was easy); facilitating condition (using FEPSim was well suited to my needs); social influence (people who are important to me think that I should use FEPSim); behavioral intention to use FEPSim (I plan to use FEPSim in the near future); and actual use of FEPSim, if applicable [22].

### Participant Timeline

This feasibility trial consists of a 10-week intervention treatment phase; this study does not have a follow-up phase. The total trial data collection period will be 9 months. As shown in Figures 1 and 2 and in Table 1, measurements will be taken at 4 points in time for each group: at baseline (week 0); during weeks 2, 4, and 8; and after the intervention (week 10).

**Figure 1 figure1:**
[figure not shown]
Flow of participants. AROM: active range of motion; PROM: passive range of motion; PRWE: patient-rated wrist evaluation questionnaire; T0: data collection point 1.

**Figure 2 figure2:**
[figure not shown]
Study design schema (primary objective and secondary objectives 1-4). AROM: active range of motion; PROM: passive range of motion; PRWE: patient-rated wrist evaluation questionnaire.

**Table 1 table1:** Key variables and measurements.

Variables			Participants		Measurement		T_0_^a^		T_1_^b^		T_2_^c^		T_3_^d^
**Primary outcome**													
	AROM^e^	Patients		Goniometer		✓		✓		✓		✓	
	PROM^f^	Patients		Goniometer		✓		✓		✓		✓	
	Grip strength	Patients		Dynamometer		✓		✓		✓		✓	
	Pinch grip	Patients		Pinch meter		✓		✓		✓		✓	
**Secondary outcomes**													
	Perceived wrist pain and disability during daily life activities	Patients		PRWE^g^ questionnaire		✓		✓		✓		✓	
**Measures of usability and technology acceptance**													
	Performance expectancy	Therapists		Semistructured interview								✓	
	Effort expectancy	Therapists		Semistructured interview								✓	
	Facilitating condition	Therapists		Semistructured interview								✓	
	Social influence	Therapists		Semistructured interview								✓	
	Behavioral intention to use the FEPSim	Therapists		Semistructured interview								✓	
	Actual use of the FEPSim	Therapists		Semistructured interview								✓	
**Measurements of economic evaluation**													
	Costs	N/A^h^		Questionnaire for costs associated with use of the FEPSim and provision of the intervention		✓						✓	
**Covariates**													
	Demographic variables	Patients		Self-report assessment questionnaire		✓							
	Medical condition (distal radial or ulnar fractures, stroke, or osteoarthritis)	Patients		Therapist records		✓							
	Whether the participant is taking any pain medication	Patients		Self-report assessment questionnaire		✓		✓		✓		✓	
	Activities the participant preforms at home or work	Patients		Self-report assessment questionnaire		✓		✓		✓		✓	

^a^T_0_: data collection point 1.

^b^T_1_: data collection point 2.

^c^T_2_: data collection point 3.

^d^T_3_: data collection point 4.

^e^AROM: active range of motion.

^f^PROM: passive range of motion.

^g^PRWE: patient-rated wrist evaluation.

^h^N/A: not applicable.

### Sample Size

#### Primary Objective and Secondary Objectives 1 to 4

As this is a feasibility study, a sample size calculation is not required [17]. However, we can estimate the number of participants we will be able to recruit during the data collection period. According to the clinical partners at the 2 hospitals involved in this study, approximately 167 patients who potentially meet the inclusion criteria will be admitted (accessible population). We aim to recruit 47 participants for each group, for a total sample size of 94 participants, to compensate for a 30% dropout rate. Thus, the recruitment of 94 participants represents 56.3 % (94/167) of the participation rate. This number is based on our ability to detect a small effect size (Cohen *d*=0.25) with 80% power and an α of .05 (two-sided). The sample size calculations were estimated using G*Power software version 3.1.9.4 (Universitat Kiel) [23].

#### Secondary Objective 6

Ten hand therapists from the hand therapy services who have used the FEPSim device will be recruited. Individual interviews will be conducted until either redundancy or theoretical saturation of the data has been achieved [24].

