### Interventions

The eligible participants will be randomly assigned in a 1:1 ratio to either the experimental group or the control group.

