### Data Analyses

#### Primary Objective and Secondary Objectives 1 to 4

Data analyses will be conducted using the intention-to-treat principle. Complete case analysis will be the primary method for dealing with missing data equal to or more than 10%. This is the most common method for dealing with missing data and reducing the risk of bias [27]. For missing data of less than 10%, we will use a simple imputation method by replacing the missing data with the average participants in the same strata (ie, medical condition). The analyses will focus on descriptive statistics and CI estimation rather than formal hypothesis testing [28]. Descriptive statistics will be used to characterize the groups at the pretest and posttest as well as during weeks 2, 4, and 8. The outcome variables as well as other data such as the length and dosage of each intervention will be summarized as n (%), mean (SD), or median (IQR), as appropriate. The retention rates, intervention compliance, and missing data will be summarized for outcomes related to the secondary objectives, which, together with the estimates, will assist in calculating the sample size for a definitive trial. As this study aims to assess the feasibility of conducting a definitive trial, clinical effectiveness is a secondary objective (ie, the study’s proof-of-concept element). In this regard, comparisons of the outcome variables at the pretest (week 0) and posttest (week 10) within the groups will be performed using a paired two-tailed *t* test (or a Wilcoxon signed-rank test if the data are not normally distributed) for AROM, PROM, grip strength, and pinch grip force and a Wilcoxon signed-rank test for the PRWE. Comparisons between the groups at the pretest and posttest will be performed using a *t* test (or a Mann-Whitney *U* test if the data are not normally distributed) for AROM, PROM, and grip strength and a Mann-Whitney *U* test for the PRWE. With our sample size, there would be a power of 0.8 to detect a medium effect size of Cohen *d*=0.25. However, we are aware that our study might be underpowered due to the sample size. If no statistically significant differences are found, our results will be classified as inconclusive rather than negative. We will report 95% CIs and interpret the level of uncertainty based on them [28]. In addition, we will explore the effects of the covariates using general linear models or multilevel mixed models when appropriate. All the α levels of significance will be set at *P*≤.05 (two-tailed).

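### The stated 80% power for d=0.25 with 94 participants does not hold for the planned between-group t test (about 22%, or 17% after dropout), and the same d is called both small and medium

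*Protocol article*

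**What the plan says.** The Sample Size section first says that a feasibility study does not require a sample size calculation and estimates how many patients can be recruited: 94 of about 167 accessible. It gives the target as "We aim to recruit 47 participants for each group, for a total sample size of 94 participants, to compensate for a 30% dropout rate". It then says that this number rests on the ability to "detect a small effect size (Cohen *d*=0.25) with 80% power and an α of .05 (two-sided"), computed in G*Power. The G*Power test family is not named.

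The Data Analyses section repeats the claim: "With our sample size, there would be a power of 0.8 to detect a medium effect size of Cohen *d*=0.25". It adds that the study might be underpowered, and that non-significant results will be treated as inconclusive.

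The same section names the tests for range of motion and strength: a t test (or Mann-Whitney U) between groups at pretest and posttest, and a paired two-tailed t test (or Wilcoxon signed-rank) within groups from week 0 to week 10. General linear or multilevel mixed models are mentioned only for exploring covariate effects. On the significance level: "All the α levels of significance will be set at *P*≤.05 (two-tailed"). Allocation is 1:1 (Interventions).

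**The concern.** A standardised difference of 0.25 is small for a trial with fewer than 50 per arm, so 80% power is implausible on sight. The claim appears twice, and the two places disagree on whether 0.25 is a small or a medium effect.

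The article did not need a power claim for a feasibility trial. Having made one, it tells readers that the clinical comparison can detect a modest effect. Anyone reading the clinical results, or using this article to plan the definitive trial, would be misled about how precise the between-group estimates will be.

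**Working it through.** **Inputs.** d = 0.25, power 80%, two-sided alpha .05, 47 per group, 30% dropout (Sample Size); 1:1 allocation (Interventions); two-sample t test between groups and paired t test within groups (Data Analyses). Completers: 94 × 0.7 = 65.8, about 33 per arm.

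**1. Attempt to reproduce the stated 80%: two-sample t test.** Noncentrality = d × √(n/2), with 2n − 2 degrees of freedom.

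| n per arm | noncentrality | critical t | power |
|---|---|---|---|
| 47 | 0.25 × √23.5 = 1.212 | 1.986 | 0.224 |
| 33 | 0.25 × √16.5 = 1.016 | 1.998 | 0.170 |

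The 80% is not reproduced. The Mann-Whitney alternative (relative efficiency 0.955) gives 21.6% and 16.4%.

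**2. Size needed for 80%.** Normal approximation: n per arm = 2 × (1.960 + 0.842)² / 0.25² = 2 × 7.85 / 0.0625 ≈ 251.2, so 252. The exact noncentral t gives 253 per arm. That is 506 in total, about three times the accessible population (506 / 167 = 3.0).

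**3. Within-group paired t test, taking 0.25 as the standardised mean change.** Noncentrality = 0.25 × √47 = 1.714, power 0.389. With 33 pairs power is 0.286. 80% needs 128 pairs. Even all 94 participants pooled as pairs give 0.670.

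**4. Other readings of the sentence.**
- One-sided two-sample test: 32.9% (47 per arm), 26.1% (33 per arm).
- 94 per arm instead of 94 in total: 40.0%.
- 0.25 meant as Cohen f, that is d = 0.5 for two groups: 66.9% (47 per arm), 51.6% (33 per arm).
- Baseline-adjusted comparison at 47 per arm, correlation assumed: 28.3% at 0.5 and 51.6% at 0.8. Reaching 80% needs a correlation of about 0.90 (0.93 at 33 per arm).

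**5. What the design can do.**
- Effect detectable with 80% power: d = 0.58 (47 per arm), d = 0.70 (33 per arm). These are 0.58 / 0.25 = 2.3 and 0.70 / 0.25 = 2.8 times the stated effect.
- 95% CI half-width for a difference in SD units = t × √(2/n): 1.986 × √(2/47) = 0.41 and 1.998 × √(2/33) = 0.49.

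**6. Labels.** Sample Size calls d = 0.25 small; Data Analyses calls it medium. This conflict needs no calculation.

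**The case against.** **The figure may come from a test that is not named.** Outcomes are measured repeatedly, and G*Power offers repeated-measures ANOVA. A group-by-time interaction with f = 0.125 (the two-group conversion d/2), 4 measurements and an assumed correlation of 0.5 gives 82.6% at N = 94, though 65.9% at N = 66. With 5 measurements and an assumed correlation of 0.6 it gives 83% even at N = 66. A between-group repeated-measures factor with f = 0.25, 2 measurements and correlation 0.5 gives 79.1% at N = 94 and 63.7% at N = 66. It follows that the documents do not support saying that no model of any kind could produce 80%.

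This does not rescue the sentence. The correlations are not in the article, and the article gives mixed models only an exploratory role. An interaction f of 0.125 is also not an endpoint d of 0.25. As an illustration, let the group difference grow linearly from 0 to 0.25 over 4 occasions. The differences are 0, 0.083, 0.167 and 0.25; their SD around the mean of 0.125 is √[(2 × 0.125² + 2 × 0.042²)/4] = 0.093; and f = 0.093 / 2 = 0.047. Power for that interaction at N = 94 and correlation 0.5 is about 16%. A mix-up of f and d is possible but cannot be shown.

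**It is a feasibility trial, and possible underpowering is conceded.** This is true and lowers the severity. Effectiveness is a secondary, proof-of-concept objective, and confidence intervals are put ahead of testing. But the caveat gives no figure, and it follows a sentence claiming 0.8. It does not correct that number.

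**Stronger conclusions that a reader might infer.**
- *Any significant result must be a large overestimate.* This depends on the unknown true effect. With 33 per arm the mean significant estimate is about 2.5 times the truth if d = 0.25, but about 1.1 times if d = 0.7. Nor does the article select estimates on significance for the definitive trial's sample size.
- *The rule on inconclusive results lets a significant one stand as positive.* The text reads "If no statistically significant differences are found, our results will be classified as inconclusive rather than negative". No rule declares a significant result positive, and 95% CIs are to guide interpretation.
- *A 40% familywise error rate (1 − 0.95¹⁰).* This assumes ten independent outcomes, whereas active and passive motion of the same joint are plainly related. Multiplicity is also a separate matter from this arithmetic.

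**Conclusion.** Wrong as written. For the named two-sided t test with d = 0.25, power is about 22% at 47 per arm and 17% at about 33 completers per arm, against a stated 80%. The first figure already credits the trial with no dropout. The calculation rests on the article's own inputs and on reading d as the between-group difference at week 10 in SD units. A baseline-adjusted analysis would do better, but would need a correlation of about 0.90 or more to reach 80%.

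The supportable claim is that the figure cannot be reproduced for the planned comparison, not that it is impossible under every model. The conflict between the small and medium labels stands by itself. Severity: should be fixed. The primary objective is feasibility, and the trial does not depend on this figure.

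**What to change.** Keep 94 participants and justify the number by expected recruitment (94 of about 167). Replace the power sentences in both Sample Size and Data Analyses, for example:

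*The sample size is set by the number of patients who can be recruited. With 47 per group, or about 33 per group after 30% dropout, the 95% CI for a between-group difference has a half-width of about 0.41 or 0.49 SD. A two-sided two-sample t test at alpha .05 has 22% or 17% power for d = 0.25, and reaches 80% power at d of about 0.58 or 0.70.*

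Delete both the small and the medium label. If the 80% came from a repeated-measures calculation, state the G*Power test family, the effect-size measure, the number of measurements, the assumed correlation and the treatment of dropout, and say that it does not apply to the t test.

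Cost: wording in two places and a less favourable stated figure. No additional patients and no change to the design.
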